	**Risk % for 2 years**		
	Aspirin*	Warfarin	Difference between aspirin and warfarin

Stroke			

All stroke	7.8	5.0	2.8
Ischemic stroke	7.4	4	3.4
Fatal ischemic stroke	0.925	0.5	0.425
Hemorrhagic stroke	0.4	1.0	-0.6
Fatal hemorrhagic stroke	0.19	0.35	-0.16
Total stroke deaths	1.15	0.85	0.3
All deaths**	10.2	9.4	0.8

Bleeds			

EC bleeding***	2	3.4	-1.4
Fatal EC bleeding	0.175	0.32	-0.145

*, Data correspond to the aspirin alone arms with exclusion of the aspirin + low-dose warfarin arms of the pooled studies; **, including stroke deaths, cardiovascular deaths, but not extracranial bleeding deaths; ***, EC = extracranial, mostly severe gastrointestinal bleeds requiring admission to hospital, 2 units of blood, or surgery.

We will present patients and clinicians with the choice between warfarin and aspirin use as we think that is the dominant choice for patients with atrial fibrillation at average risk of stroke. For a group, perhaps as large as 20% of patients with atrial fibrillation (i.e., young patients without hypertension, diabetes, or previous stroke) the pertinent choice may be between aspirin and no antithrombotic therapy [26]. This group will not be represented in our intended sample of patients (i.e., individuals at risk of atrial fibrillation > 60 years-old, with hypertension, diabetes, or previous cardiovascular events). Adding this choice (or the choice of warfarin vs. no antithrombotic therapy) to the probability trade-off would require more time than feasible during clinician interviews. More importantly, the choice between warfarin and aspirin is most likely to demonstrate omission bias (physicians may place a relatively higher value on avoiding a bleed than on avoiding a stroke because they do not witness the strokes they have prevented) or differences in values and preferences between patients and clinicians, if these were present. Therefore, we will limit the probability trade-off exercises to the choice of warfarin vs. aspirin.

#### The feeling thermometer

To further understand the treatment preferences elicited using the probability trade-off and capture the values patients and clinicians place on the health states that may result from their choice, namely strokes and bleeds, we will conduct preference-elicitation exercises using the feeling thermometer, a visual analogue scale [27,28]. When completing the feeling thermometer patients choose the score on the thermometer that represents the value they place on the health state they are being asked to evaluate. The feeling thermometer is anchored at death (0) and perfect health (100). The feeling thermometer will allow us to check understanding of the relative severity of the health states in question (i.e., patients should assign a lower value (a value closer to 0) to a major stroke with severe and permanent disability than a minor stroke).

Because the visual analogue scales may be prone to context bias, that is rating of one state may influence rating of other states [29,30], we will randomize the order in which participants will consider the health states to minimize this bias. We will ask participants to consider the following health states one at a time on the feeling thermometer:

▪ Major and minor strokes. We will inform patients that the sequelae of the stroke will last for the patient's life expectancy.

▪ Severe bleed. We will inform patients that they will have a major bleed within the first year of taking the antithrombotic agent but will not have another severe bleeding event for the rest of their life

▪ Taking warfarin

▪ Taking aspirin

### The second phase: the focus groups

Qualitative research methods are well suited to study personal meaning, perceptions, beliefs, and values [31]. These methods are therefore appropriate to provide clinicians and patients with the opportunity to make explicit the thinking process, and explore the various hypotheses suggested as to why participants hold the views they do. Individual in-depth interviews and focus groups could provide this information. The individual clinician interviews will create an appropriate mindset for participants to consider in the focus groups *why *they hold the views they do. An important advantage of focus groups over in-depth personal interviews is the opportunity to explore dynamic interactions among the group members. These interactions include sharing of ideas and insights, stimulating others to consider the issues that may underlie their own preferences, and exploring areas of consensus and dissensus [32].

Thus, the focus groups are most likely to offer plausible explanations of clinicians' and patients treatment choices and the reasons for any inconsistency of these choices with their utilities for the health states of interest. If our results of the first phase confirm our preliminary findings, then these explanations will shed light on differences in preferences between clinicians and patients.

#### Setting and participants

At each of the 3 sites we will convene focus groups of clinicians and patients. We will follow the recommendation to keep the focus groups as homogeneous as possible in terms of preferences regarding the bleeding threshold [32]. To the extent that group members perceive others around the table as similar to themselves, they may feel safe to express themselves while expecting understanding and respect from the other members. We plan to convene six focus groups in total (3 of clinicians and 3 of patients). These numbers relate to our experience with focus groups and their information yield and to what is feasible for this proposal. Members of the focus group will be recruited from phase I to represent different preferences

#### Group configuration and data collection

Each group will have 10 participants per session, a trained facilitator (a clinician) and an expert assistant (not a clinician) [32]. The facilitator leads the focus group, facilitates the group ensuring that all participate, ensures that the group completes the agenda on time, and monitors and manages the group dynamic. The assistant (i.e., an expert qualitative researcher) will participate in all focus groups at all site and will document seating arrangements, the first words of each member, take notes on interaction dynamics and nonverbal behaviors, and operate the tape recorders. A digital tape recorder (and a backup) equipped with tabletop microphones will document all acoustic data for later transcription. The setting will be a small conference room in the hospital or primary care center. We will pay particular attention to issues related to noise, will limit interruptions once the focus group dynamic begins, and will keep the meeting on time. Participants will spend about 90 minutes discussing the agenda described in the following section.

#### Focus group agenda

The goals of the focus group are to educate the members about the results of the individual interviews, and to explore why clinicians and patients have the preferences they do. The facilitator will first ask about this in an open ended way, allowing participants to express their views in their own words in order to explore what reasons they give. Another goal of the focus groups is to get members to make explicit their thinking process that led to those preferences, and to explore the various hypotheses suggested (e.g., omission bias, avoidance of clinician-associated risk) as to why clinicians hold the views they do. The facilitator will start the proceedings by setting ground rules, making introductions, and using warm-up exercises to set a comfortable and open environment for exchange of ideas.

To achieve the research goals of the focus group, the facilitator will guide focus group members through a structured process: The facilitator will first present results from the individual interviews. Aggregate data will be presented and in addition, each participant will receive the results of their individual responses during the preference elicitation exercises. The facilitator will then elicit member responses to open-ended questions that he will pose to the group about these findings. For example, the facilitator will check that group members understand the findings before further discussion. Then, the facilitator will ask whether group members are surprised about the findings and if so, why or why not. They will be asked to comment on why they hold the particular treatment preferences expressed in the individual exercises. This will be followed with more structured elicitation exercises. The facilitator will contrast the results of the treatment preference exercise with the results of the feeling thermometer exercises to the extent that these exercises reveal, on average, different apparent values placed upon the health states. In addition, the following contrasts will be presented to initiate or continue discussion with the group:

▪ Direct contrast of the choices and strength of preferences for antithrombotic treatment of the average clinician in the focus group and of the average patient in the study (i.e., the number of additional bleeds that clinicians and patients are willing to tolerate to prevent an additional stroke at the point of indifference between using warfarin and using aspirin).

▪ Direct contrast of the average utilities for stroke, bleeding, and using antithrombotic agents between patients and clinicians.

To promote and focus debate the facilitator may ask the following questions to the group (if appropriate given the results):

▪ Can you describe, in your own words, the thought processes you went through in making your decisions during the probability trade-off and feeling thermomether exercises?

▪ Do you think that your answers to probability trade-off and feeling thermomether are consistent with each other? Why or why not?

▪ Which one of the exercises (probability trade-off, feeling thermomether) do you think captured more accurately the true relative values you place on avoiding bleeds and preventing strokes? Why?

Depending on the results during phase 1 (individual interviews), other questions could be relevant, including the following:

▪ You placed a relatively higher value on bleeding and a relatively lower value on stroke when making a decision (probability trade-off) than when we looked at those outcomes separately (feeling thermomether). Why?

▪ Can you think of plausible explanations for the differences between clinicians and patients choices and preferences for treatment?

▪ Can you think of plausible explanations for the differences between the answers that clinicians gave when they participated as patients and when they participated as clinicians?

### Analysis plan

#### Research question 1

When assessed systematically, do patients' and clinicians' preferences explain the apparent underutilization of warfarin to prevent strokes associated with atrial fibrillation?

##### Description of treatment preferences

We will use probability trade-off results to determine the number of additional bleeds that participants are willing to tolerate per stroke prevented with warfarin at the point of switch to aspirin. We will call this variable *b*. We will describe the distribution of *b *in clinicians grouped by age, gender, years in practice, specialty, experience with atrial fibrillation, experience with bleeds and strokes, and whether they participated as clinicians or as patients. We will also describe *b *in patients grouped by age and gender, and by personal knowledge of someone who had a major or a minor stroke, or a major gastrointestinal bleed. We will also describe the distribution of *b *in clinicians and patients by site. We will conduct exploratory linear regression analysis using *b *as the dependent variable and clinician characteristics listed above as the independent variables. The results of this analysis will guide our choices for subgroup analyses to answer Research Question 2.

#### Research question 2

To what extent do patients' and clinicians' treatment preferences differ?

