##### Differences in treatment preferences between patients and clinicians

We will test the difference of the means of *b *between the patients (*b*_*p*_) and clinicians (*b*_*c*_) using an unpaired *t *test. The observed distribution of *b*_*p *_in our preliminary work was highly skewed. This was because patients clustered at the highest *b *offered. For this study, we propose to offer a maximum *b *that is twice as large as the maximum *b *offered in our preliminary study. Furthermore, we will be studying a relatively large number of patients and clinicians with distribution of the means approximating the normal distribution with SEM = SD/vn. Our sample sizes will be considerably larger than 30, a size which is often taken as a guideline threshold, above which the sample distribution of the sample mean will be reasonably normally distributed, even if the distribution of individual values is substantially skewed. Thus, the use of the t-test is appropriate. However, we will also use the Mann-Whitney test, a non-parametric test that does not require the assumption of normality of the distribution. After identifying pertinent subgroups in the analysis to Research Question 1, we will conduct modified *t *tests to test the difference of the means of *b *between the patients and the subgroup of clinicians of interest. A modified *t *test is based on the pooled estimate of variance from all the subgroups [33]. The resulting *P *values can be adjusted for multiple comparisons using the Bonferroni method (multiplying the resulting *P *value by the number of paired comparisons performed).

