We will also determine the proportion of patients and clinicians who would choose to take or recommend warfarin when b = 0.5 (that is, when patients experience one bleed for every two strokes prevented). We designate this value of b as *b*_*RCT *_because it is the average number of additional bleeds per stroke prevented reported in randomized trials of warfarin vs. aspirin from the meta-analysis [11] (Table 1). We will test the difference in these proportions using Fisher's exact test and will estimate the exact 95% confidence interval of the odds ratio for the proportions of patients and clinicians who would use warfarin at *b*_*RCT*_. We will also determine the proportion of clinicians from pertinent subgroups (identified in Research Question 1) who would choose to recommend warfarin at *b*_*RCT *_= 0.5. Then, we will test the differences between this proportion and the proportion of clinicians not in the subgroup recommending warfarin when *b *= 0.5, as well as the difference between the proportion recommending in the subgroup and the proportion of patients who would choose to take warfarin at *b*_*RCT*_.

#### Research question 3

What explains any differences in treatment preferences between patients and clinicians?

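### Clinician subgroups are chosen by regressing b on clinician characteristics and then tested on the same b data, with an optional Bonferroni step that counts only the tests performed

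*Protocol article*

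**What the plan says.** **Selection (Research question 1, Description of treatment preferences).** The grouping planned for describing b is this: "clinicians grouped by age, gender, years in practice, specialty, experience with atrial fibrillation, experience with bleeds and strokes, and whether they participated as clinicians or" (the quote stops just before the second of the two role instructions). That is seven characteristics, or eight if bleeds and strokes are counted separately or site is added. Then: "We will conduct exploratory linear regression analysis using *b *as the dependent variable and clinician characteristics listed above as the independent variables". The use of that regression is explicit: "The results of this analysis will guide our choices for subgroup analyses to answer Research Question 2".

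**Testing (Research question 2).** On mean b: "After identifying pertinent subgroups in the analysis to Research Question 1, we will conduct modified *t *tests" of patients against the clinician subgroup of interest. "A modified *t *test is based on the pooled estimate of variance from all the subgroups". On acceptance at b = 0.5, the subgroup's proportion is compared with "the proportion of clinicians not in the subgroup recommending warfarin when" b = 0.5, and with the proportion among patients.

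**Adjustment (Research question 2).** "P *values can be adjusted for multiple comparisons using the Bonferroni method". The multiplier is the number of paired comparisons performed. The paragraph on proportions states no adjustment.

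**Power (Sample size estimation).** At least 80% power is claimed for a difference of 0.75 SD between 96 patients and clinician subgroups of 20 or more.

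The protocol gives no fixed subgroup list, no threshold for choosing a subgroup and no split of the sample.

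**The concern.** A characteristic stands out in the regression because clinicians in one of its levels have, partly by chance, unusually low or high b. Testing that same level on b, or on b cut at 0.5, uses the same chance deviation again. The test statistic no longer has its nominal null distribution.

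Bonferroni by comparisons performed does not repair this. The characteristics screened and dropped are not counted, although they are what made a chance finding likely. The adjustment is also permissive, and it is not stated for the proportion tests.

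At stake is the reading of Research question 2 by subgroup. A statement that one specialty or age band is significantly more bleeding-averse could rest on a P value that overstates the evidence, and the estimated difference would tend to be too large.

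**Working it through.** **Inputs.** From the protocol: 96 clinicians, 96 patients, α = 0.05, subgroups of at least 20, and seven or eight characteristics. The 0.63 acceptance rate used in one set of runs is the clinician proportion in Sample size estimation. Assumed, because the protocol does not fix them: the selection rule, binary coding, independence of the characteristics, and Fisher's test for the subgroup proportions.

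**1. Reproduce the stated power.** With z the two-sided critical value, power = Φ(d·√[n₁n₂/(n₁+n₂)] − z).
- 96 vs 96 at 0.4 SD: 0.4 × √48 − 1.960 = 0.811, power 0.791. Table 2 gives .79. All 16 cells of Table 2 reproduce closely.
- 20 vs 96 at 0.75 SD: 0.75 × √16.55 − 1.960 = 1.091, power 0.862. The claim of at least 80% is right, but at an unadjusted 0.05.

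**2. How much the selecting and testing contrasts share.** For a subgroup of n₁, with n₂ other clinicians and m patients, take the contrasts subgroup minus other clinicians and subgroup minus patients. Under equal variances their correlation is (1/n₁) / √[(1/n₁+1/n₂)(1/n₁+1/m)].
- n₁ = 20, n₂ = 76, m = 96: 0.0500 / √(0.0632 × 0.0604) = 0.81.
- n₁ = 48, n₂ = 48, m = 96: 0.0208 / √(0.0417 × 0.0313) = 0.58.

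Selecting on the first contrast therefore carries strongly into the second, although the patients play no part in the selection.

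**3. Chance that the regression offers something under the null.** For independent characteristics this is 1 − 0.95ᴷ: 30% for K = 7 and 34% for K = 8. Simulated: 29% and 32%.

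**4. Error rates of the planned tests.** Simulated under a global null, with independent binary characteristics. The ranges cover K = 7 to 8 and different assumed distributions of b.

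| Planned test | Strongest characteristic always tested | Only characteristics with regression P < 0.05 tested |
|---|---|---|
| Either level vs patients, mean b, unadjusted | 27–28% | 12–17% |
| Same, Bonferroni by tests performed | 15.5–16.4% | 7–11% |
| Subgroup vs other clinicians, Fisher at b = 0.5 | 12–16% | 7–11% |

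A threshold of P < 0.10 gives 20.5–22.2% unadjusted and 10.5–11.1% with Bonferroni for either level vs patients.

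Under a threshold rule these figures include runs in which nothing is selected. In the runs with K = 7 and P < 0.05, a subgroup is selected in 29.1%. Given that, either level differs from patients in 50.1%, and 0.291 × 0.501 = 14.6%, which lies within the table's 12–17%.

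**5. Source of the inflation.** A single subgroup named in advance gives 4.9–5.1%. One characteristic named in advance, both levels against patients with Bonferroni × 2, gives 4.8–4.9%. The excess comes from selection.

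**6. Power after adjustment, 0.75 SD.**
- 20 vs 96: 0.791 with two comparisons (z = 2.241), 0.745 with three (z = 2.394), 0.641 with seven.
- 48 vs 96: 0.75 × √32 − z = 4.243 − z, giving 0.977 with two and 0.968 with three.

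Groups of 48 assume equal allocation to the two role instructions, which the protocol does not state.

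**The case against.** **The main result does not depend on this step.** This stands. The comparison of all patients with all clinicians, and the sample size built on it, do not use the subgroup selection.

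**The regression is labelled exploratory and its candidates are listed in advance.** True, but the label covers only the regression. The tests that follow are presented as answers to Research question 2, and the subgroup comparison with patients carries a power claim at 0.05.

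**The rates depend on a rule the protocol does not state.** This stands. The text says only that the regression guides the choice, so testing no subgroup is possible. Age and years in practice will be correlated. With two correlated pairs among seven characteristics and a P < 0.05 rule, the rates fall to 11.5% unadjusted, 6.6% with Bonferroni, and 5.8% for the Fisher test. A reader might infer that error is several times 5% under any reading of the plan. That holds only for some selection rules, and with Bonferroni the excess can be small.

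**The null for subgroup against patients conflicts with the authors' expectation.** Their earlier means (SD) of b are 2.2 (0.9) in patients and 1.3 (0.8) in clinicians, and the Discussion expects substantially different choices. If so, rejecting that null is correct, and the harm is exaggeration of the difference in a selected subgroup. The test against other clinicians stays inflated.

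**A larger figure should not be used.** Selecting the strongest characteristic and testing mean b between the subgroup and other clinicians gives about 29–34% error. The plan contains no such test: mean b is tested only against patients, and the contrast with other clinicians is on proportions.

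**Details may sit in a fuller plan.** A fixed subgroup list may. But selecting and testing on the same data, and permissive adjustment, are choices this document states.

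**Conclusion.** The concern holds within limits. As written, the subgroup P values under Research question 2 are not valid at their nominal level, and the Bonferroni step would not make them so even if applied. Under a global null with independent characteristics, error against patients is about 12–28% unadjusted and 7–16% with Bonferroni by tests performed. The proportion test against other clinicians runs at about 7–16%. The position in these ranges depends on the selection rule, the coding of characteristics and the acceptance rate at b = 0.5. Correlated characteristics can bring the rates below them.

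Nothing here supports the inference that the overall patient–clinician comparison is compromised, or that a spurious subgroup will necessarily be reported. In most null runs, no subgroup differed significantly from patients. This is a correction to a secondary analysis that should be made before the data are seen.

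**What to change.** 1. Name randomised role (answering as patient or as clinician) and specialty as the confirmatory clinician subgroups. Role is assigned by the design partly to study its effect, and specialty is built into recruitment and the focus groups.
2. State that P values will be adjusted, by Bonferroni or Holm, across all comparisons of these subgroups, including the proportion tests at b = 0.5.
3. Report any other subgroup suggested by the regression with estimates and confidence intervals only, labelled hypothesis-generating.
4. Restate the subgroup power. For 20 clinicians vs 96 patients at 0.75 SD it is about 0.79 with two comparisons and 0.75 with three, or state it for the larger prespecified groups.

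**Cost.** Items 1–3 are changes of wording and need no new data. The real cost is power in small subgroups, and it grows with the family. Both levels of two binary characteristics, with mean b vs patients (4), proportion vs patients (4) and proportion vs other clinicians (2), make 10 comparisons. At 0.05/10 (z = 2.807), power for mean b at 0.75 SD is Φ(3.051 − 2.807) = 0.60 for 20 clinicians and Φ(4.243 − 2.807) = 0.92 for 48. The family should therefore be kept short and its size stated. Multiplying by every subgroup screened would also control error, but it over-corrects (about 2.7–2.9% for all levels of seven or eight characteristics) and costs more power.
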